### Sample size

Since this study is not testing a statistical hypothesis, but rather exploratory, it is decided to proceed with the minimum number of subjects empirically required within the limit that satisfies the purpose of the study. In general, it should be considered that such exploratory research is usually conducted with around 50 people. Most high-risk pregnant women do not want to visit the hospital after childbirth, so when obtaining consent in advance, patients who have actively consented to long-term observation should be registered. Therefore, it was determined that 12-month observation data could be collected from 150 subjects when about 300 subjects were recruited by calculating the dropout rate as about 50%. Separately, this study checked the health of mothers and newborns before and after pregnancy and considered that most complications such as gestational diabetes occurred within 2 years after childbirth. Accordingly, this study is continuously necessary for a total of 3 years, about 1 year including the entire period of pregnancy, and 2 years to confirm the occurrence of complications and childbirth results as a follow-up. Therefore, about 150 women will receive relevant clinical data every year, and 500 mothers in total will be selected as target subjects.

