### Outcome measure

Table 3 shows the intervention and control groups measured item results, and the same items will be measured after the 6-week study participation period. Primary measurements will include weight, blood pressure, blood sugar and health literacy, and physical and obstetric characteristics. In addition, character, exercise and nutritional information on basic demographic characteristics and basic psychological state will be collected. For the primary measurement, the same information will be collected for both the primary and final results for comparison with the final result.

**Table 3 Tab3:** Outcome measure items

1	Weight, blood pressure, blood sugar measurement
2	Health information literacy
3	Physical and obstetric characteristics (including height, weight, gestational age, date of birth, etc.)
4	Basic demographic characteristics (spouse, marital status, economic status, etc.)
5	Basic psychological status (prenatal-postpartum depression questionnaire, high-risk-related trauma questionnaire, anxiety, and psychological state)
6	International Physical Activity and Exercise Questionnaire (IPAQ)
7	Nutrition and Dietary Questionnaire
8	Newborn information data (weight, head circumference, pregnancy method, birth period, etc.) (after 6 weeks/in case of delivery)
9	Questions for high-risk mothers
10	Smartphone app evaluation questionnaire (only intervention group)
11	App usage effect confirmation questionnaire (only intervention group)
12	Self-report (only intervention group)

Items 1 to 9 in Table 3 are for the intervention and control groups measurement. Item 1 measures body weight, blood pressure, and blood sugar daily during the study period. The amount of change from the start to the end of the study will be evaluated. Item 9 is about high-risk mothers and asks them to check for the diseases that apply to them, such as gestational hypertension, gestational diabetes, and prenatal-postpartum depression. This item will be completed at the beginning and end of the study. When the study is over, it will also be checked whether the disease is maintained. This can help with the prevalence and maintenance of healthcare-related diseases.

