On the other hand, to check changes in health behaviors, the International Physical Activity Questionnaire (IPAQ) [26] is used to evaluate changes in health behaviors with a questionnaire verified in the pregnancy cohort. In addition, the results of maternal nutrition and diet measure the change in health behavior toward diet and nutrition by comparing before and after the mother’s recorded eating habits and nutrition and dietary behavior questionnaires.

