### Statistical analysis

This study will compare the outcomes between the two groups using IBM SPSS software for statistical analysis. For this purpose, descriptive statistics and correlation analysis of each group are performed, and a paired sample T-TEST of two groups is performed, so that comparative analysis can be performed. In addition, pre-post-group comparison analysis will be conducted, especially for both groups, from the first outcome to the final outcome. Hierarchical and stepwise regression analyzes will be conducted to determine the impact of each item to look at changes in health behavior as the end result.

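### Stepwise regression is planned to show which items drive behaviour change; its results for selected items will be too optimistic, and the text leaves the randomised arm's place in the model open

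*Protocol article*

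**What the plan says.** The Statistical analysis section opens with the purpose: "This study will compare the outcomes between the two groups using IBM SPSS software for statistical analysis". It gives the two-arm comparison to a t-test ("a paired sample T-TEST of two groups is performed, so that comparative analysis can be performed") and a pre-post comparison. It then adds a regression step: "Hierarchical and stepwise regression analyzes will be conducted to determine the impact of each item to look at changes in health behavior". Behaviour change is named there as the end result.

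Outcome measure says what that result is. For physical activity, the IPAQ "is used to evaluate changes in health behaviors with a questionnaire verified in the pregnancy cohort"; for diet, eating records and questionnaires are compared before and after.

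The items are presumably those of Table 3. "Items 1 to 9 in Table 3 are for the intervention and control groups measurement". Items 10 to 12 exist in one arm only; item 11, for example, reads "App usage effect confirmation questionnaire (only intervention group".

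The article does not list the candidate variables, give entry or removal limits, or say whether the randomised arm is in the model. Sample size describes the study's status this way: "Since this study is not testing a statistical hypothesis, but rather exploratory".

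**The concern.** The article names a method and gives it an inferential job, to determine impact. Stepwise selection cannot do that job. It keeps variables because their p-values are small in these data, so the p-values and intervals printed afterwards ignore the search, and the coefficients lean away from zero. An analysis plan that followed this sentence would inherit the problem.

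Two further risks depend on how the sentence is carried out:

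- **The arm.** If it is offered to the procedure as one candidate among many, it can be removed. When it survives, its estimate has been filtered for being large.
- **The app-only items.** If items 10 to 12 were entered in a model for both arms fitted to complete cases, every control would be excluded and the arm effect could not be estimated.

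At stake is a published list of drivers of health behaviour, some of them spurious, and possibly a missing or inflated estimate of the app's effect on behaviour.

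**Working it through.** **Inputs from the article.** Total sample: "about 150 women will receive relevant clinical data every year, and 500 mothers in total will be selected as target subjects". Dropout is about 50%, allocation is 1:1, and Table 3 has 12 items, 9 of them measured in both arms.

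**The plan's own figure.** No figure is given for the regression. The nearest is recruitment: 150 / (1 - 0.50) = 300, which agrees with Sample size. The same loss applied to the total gives 500 x 0.50 = 250. That dropout rate is stated for 12-month data, not for the 6-week endpoint, so N = 250 is an assumption. The range 150 to 500 is shown.

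**Assumptions, since the article gives none.** Entry at p<0.05, removal at p>0.10, arm plus 9, 15 or 20 covariates with pairwise correlation 0.2, and 2,000 simulated trials per setting. Effects are in residual SD units.

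**1. Spurious items, no true effects.** With k independent candidates, P(at least one selected) is roughly 1 - 0.95^k.

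| Candidates k | 1 - 0.95^k | Simulated, N = 150 to 500 |
|---|---|---|
| 9 | 37% | 35-37% |
| 15 | 54% | about 50% |
| 20 | 64% | 58-60% |

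Items 6 and 7 are themselves the behaviour outcomes. Taking both out leaves 9 - 2 = 7 items common to both arms, and 1 - 0.95^7 = 30%. Several of those items bundle many variables (item 4 covers spouse, marital and economic status), so the real count may well be higher.

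**2. The arm, if it is an unforced candidate.** 15 covariates, 3 of them with real effects (coefficient 0.2 each). Each cell gives the share of trials in which the arm is dropped, then the mean estimate when kept divided by the truth.

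| N | 0.1 SD | 0.2 SD | 0.3 SD | 0.5 SD |
|---|---|---|---|---|
| 500 | 81%; 2.2 | 39%; 1.27 | 9%; 1.07 | 0%; 1.00 |
| 250 | 88%; 3.1 | 68%; 1.72 | 34%; 1.24 | 2%; 1.02 |
| 150 | 91%; 3.8 | 79%; 2.1 | 56%; 1.5 | 18%; 1.1 |

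At N = 250, the nominal 95% interval for a kept arm covers the truth in 71%, 91%, 96% and 97% of trials across these four effects. With no true effect, the arm is selected in 4.0-5.4% of trials, so its type I error stays near nominal: randomisation makes it independent of the covariates.

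**3. The same data with the arm forced into a fixed model of all 15 covariates.** At N = 250 the mean estimates are 0.099, 0.197, 0.302 and 0.504 for true effects of 0.1, 0.2, 0.3 and 0.5. Type I error is 4.3-5.4%. At 0.2 SD the forced arm is significant in 31% of trials, against 32% kept by stepwise. Stepwise therefore costs little power. What it loses is the estimate and interval in the trials where the arm is not significant.

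**4. Items 10 to 12.** These are missing by design for all controls. A complete-case model containing any of them retains app-arm women only, so arm is constant and its coefficient is undefined. No simulation is needed.

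**The case against.** The other side has a good deal to say, and most of it limits the point without removing it.

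- **The study calls itself exploratory and tests no hypothesis.** This lowers the harm, because no confirmatory claim or alpha rests on the regression. It does not make post-selection p-values valid, and the stated purpose is still to determine impact.
- **Candidate lists, limits and forced terms belong in a fuller document.** True, and their absence is not the complaint. Stepwise selection itself is stated in the article.
- **A reader might infer that this is the only analysis of the trial's aim.** The text does not support that: the same section assigns the two-arm comparison to a t-test and a pre-post comparison. Whether a paired test suits two independent arms is a separate matter.
- **A reader might infer that the plan will drop the arm or overstate the app effect.** The article never makes the arm a candidate; it speaks of items, and the arm is not a Table 3 item. Hierarchical regression is also planned, and one of its blocks could hold the arm in. The risk is open, not shown.
- **A reader might infer that the controls will be lost.** Table 3 marks items 10 to 12 as app-only, and nothing says they enter a pooled complete-case model.
- **An arm-plus-baseline model answers a different question from the impact of each item.** This stands, and the fix therefore keeps a place for item effects.

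**Conclusion.** The point holds for the selected items. Stepwise selection, as stated, will make their p-values, intervals and coefficients too optimistic. With no true effects, the chance of at least one spurious driver is about 35% to 60% for 9 to 20 candidates, given the assumed entry limit of 0.05.

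For the arm, the conclusion is conditional on its being an unforced candidate. The drop rate then runs from 0% to 91% and the inflation from 1.0 to 3.8 times, depending on assumed effect and sample size. The problem is material for small effects and negligible at 0.5 SD with 250 to 500 women. The arm's own type I error is not at issue. Loss of the controls through items 10 to 12 would follow only from a pooled complete-case model, which the article does not state.

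**What to change.** Drop stepwise selection from the Statistical analysis section and state instead:

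1. For each behaviour outcome (IPAQ, diet), one pre-specified linear model of the 6-week score on arm (always kept), baseline score, the randomisation strata and a short fixed list of baseline covariates.
2. The impact of individual items from hierarchical blocks whose content and order are fixed in advance, with arm forced in, and labelled exploratory.
3. Table 3 items 10 to 12 analysed descriptively in the app arm only.

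The same software serves, and Trial status says recruitment had not begun. The sponsor must choose the covariates and blocks beforehand, which is slightly more than a change of wording. What is lost is the automatic list of influential items, which would not have been reliable.

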### Allocation of participants

The participants will be randomly assigned in the intervention group applying the app and the general control group providing the paper guidelines performed using computer-generated assignments in a 1:1 ratio. Considering the characteristics of the intervention, both the participants and researchers will aware of the group to which they will be assigned. In addition, this study will be conducted as a stratified block. Accordingly, the registration of participants and the assignment of interventions will be performed by the medical staff, and a random number table will be generated through a computer program to assign and enroll participants in the study.

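### Stepwise regression, one of two regression methods named, should not supply the effect of each item on health behaviour

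*Protocol article*

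**What the plan says.** The Statistical analysis section of the protocol article opens with a two-group comparison: "This study will compare the outcomes between the two groups using IBM SPSS software for statistical analysis". After the descriptive, correlation and pre-post analyses it adds the regression: "Hierarchical and stepwise regression analyzes will be conducted to determine the impact of each item to look at changes in health behavior". Two methods are therefore named side by side for one aim. The section does not say which of them supplies the reported effect of an item.

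The Outcome measure section lists 12 items in Table 3 and states: "Items 1 to 9 in Table 3 are for the intervention and control groups measurement". Items 10 to 12 exist in the intervention group only. Change in health behaviour is to be measured with the physical activity questionnaire (IPAQ) and the nutrition and diet questionnaires, completed before and after.

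The Sample size section describes the study's status: "Since this study is not testing a statistical hypothesis, but rather exploratory". It also gives the target: "500 mothers in total will be selected as target subjects".

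**The concern.** The stated aim is the impact of each item. Stepwise selection answers a different question, namely which subset survives a data-driven search. This has three consequences for the per-item effects.

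- An item that is not selected has no coefficient in the final model, so a reader cannot tell a small effect from an imprecise one.
- A weak or moderate item enters mostly in samples where its estimate happens to be large, so its reported effect tends to be too big.
- The p-values and intervals printed for the final model treat the chosen set as if it had been fixed beforehand, so they understate the uncertainty.

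At stake is the table of determinants of behaviour change. If the stepwise output fills it, modest influences on exercise or diet will be either absent or exaggerated.

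**Working it through.** **Inputs from the article.** Hierarchical and stepwise regression in SPSS, with no entry or removal rule stated (Statistical analysis). Nine items measured in both arms (Outcome measure). Target of 500 women; about 300 recruited to give 150 with 12-month data at about 50% dropout (Sample size).

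**The article's own figure.** 150 / (1 − 0.50) = 300, which matches the stated 300. The point does not depend on it. It only helps to frame a range for the number analysed, since that 50% concerns 12-month observation and the number analysed at 6 weeks is not given.

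**Assumptions, not in the article.** Entry at p<0.05 and removal at p>0.10. Nine single-column candidates. True standardised effects of 0.30, 0.20, 0.10, 0.10, 0.05 and four zeros. Residual SD 1. Correlation between items 0 or 0.3. N of 150, 250, 300 and 500 analysed. Nine is a working count: some Table 3 items bundle several measures, and item 8 (newborn data) is not a start-of-study item.

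**Step 1, hand check.** For an item uncorrelated with the rest, se = 1/√N and c = 1.96 − β/se. The chance of being kept is about P = P(Z > c). The mean estimate when kept is about β + se × φ(c)/P. With β = 0.10:

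- N=150: se = 0.0816, c = 1.96 − 1.225 = 0.735, P = 0.231. Mean = 0.10 + 0.0816 × 0.3045/0.231 = 0.21.
- N=250: se = 0.0632, c = 1.96 − 1.581 = 0.379, P = 0.352. Mean = 0.10 + 0.0632 × 0.3713/0.352 = 0.17.
- N=500: se = 0.0447, c = 1.96 − 2.236 = −0.276, P = 0.609. Mean = 0.10 + 0.0447 × 0.3840/0.609 = 0.13.

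**Step 2, simulation.** Stepwise selection was compared with one model holding all nine items, with 600 data sets per setting. Ranges span the two correlations.

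| N | True effect | Kept | Mean when kept | Mean, all items in model |
|---|---|---|---|---|
| 150 | 0.05 | 10–14% | 0.18–0.22 | 0.048 |
| 150 | 0.10 | 22–27% | 0.21–0.25 | 0.098–0.109 |
| 150 | 0.20 | 65–67% | 0.25–0.27 | 0.202–0.205 |
| 150 | 0.30 | 91–94% | 0.31–0.35 | 0.298–0.304 |
| 300 | 0.10 | 36–42% | 0.15–0.18 | 0.098–0.102 |
| 500 | 0.05 | 18–21% | 0.11–0.13 | 0.049–0.051 |
| 500 | 0.10 | 55–65% | 0.13–0.15 | 0.101–0.102 |
| 500 | 0.20 | 98–99% | 0.21 | 0.201–0.204 |
| 500 | 0.30 | 100% | 0.30–0.31 | 0.300–0.301 |

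A separate run at N=250 kept the 0.10 item in about 36% of data sets, with a mean of about 0.18. This agrees with the hand check.

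**Step 3, what this means for reporting.** An item with a true effect of 0.10 has no estimate in about 100 − 22 = 78% of studies at N=150 and 100 − 62 = 38% at N=500. When it is reported, the inflation is about 0.21/0.10 = 2.1-fold at N=150, 0.18/0.10 = 1.8-fold at N=250 and 0.13/0.10 = 1.3-fold at N=500. The nominal 95% interval of a kept item with true effect 0.05 covers the truth in 54–88% of cases across N=150 to 500.

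**The case against.** The strongest reply is that the same sentence names hierarchical regression, which enters items in blocks set by the analyst and can estimate all of them. That stands. A reader might infer that the plan as a whole cannot deliver an effect for each item, but the article does not support this. The defect lies in the stepwise part and in leaving open which method fills the results table.

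Second, the study is declared exploratory, and a condensed article may leave the entry rule, candidate list and block order to the full protocol or analysis plan. Both points are fair. Their absence is not criticised here, and the exploratory label lowers the weight of the point. The label does not make a selected subset suitable for estimating each item.

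Third, several larger harms are tempting to add and do not hold:

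- *Every kept item is overstated.* Strong items at N=500 show little or no inflation.
- *Stepwise produces extra false determinants.* With only null items, the chance of flagging at least one is ordinary multiplicity. At N=250 the full model flags one in 33% and 44% of runs for 9 and 12 items, and stepwise in 33% and 47%.
- *The treatment arm may be dropped.* The article does not make arm a stepwise candidate and states the group comparison separately. Missing a modest arm effect would be low power under either model.
- *The start value is tied to change.* This is true of any change score and is not caused by stepwise.
- *The regression is the main result.* The words about the end result most naturally describe the dependent variable. They do not rank the regression above the group comparison.

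**Conclusion.** The point holds in a limited form and is minor. Stepwise selection is a planned method that does not suit the stated aim, and it should not supply the per-item effects. The harm falls on weak and moderate items and shrinks as the number analysed grows.

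The absence of estimates for dropped items follows from the method itself. The sizes rest on the assumed selection limits, nine candidates, the assumed effects and the range of 150 to 500 women analysed; none of these except the 500 target and the count of nine both-arm items comes from the article. The use of a p-value rule is itself inferred from ordinary stepwise practice.

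**What to change.** Delete stepwise from the Statistical analysis section. Keep the hierarchical regression as one model, listed in advance, for each behaviour outcome (IPAQ, and the nutrition and diet questionnaires). Use only start-of-study items measured in both arms, so Table 3 items 10 to 12 are not candidates. Force in the start value of the outcome, the arm and the stratification factors, and enter all listed items whatever their p-values. Report every coefficient with its 95% CI, including those near zero, and label the results exploratory.

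The change uses the same data and software and alters wording only; the Trial status section says the trial has not started. The price is fewer items that can be called significant determinants. The full model does not remove multiplicity, which is why the exploratory label must stay on the table.

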## Discussion

This randomized controlled trial aimed to change the health behavior of high-risk mothers by providing health care information services through the development of a smartphone app. This research can be said to be the safest and most suitable research in the present, where smart medical technology is considered more important than mHealth technology. In addition, a smartphone app can be used by anyone and anywhere, promoting a healthier and more adaptive life and playing a big role in preventing diseases.

Therefore, this study will significantly help mothers and newborns in maintaining a healthy life during and after pregnancy. In addition, if this app is used properly in actual clinical sites and the general community, this smartphone app is expected to play a very useful role for medical staff. The accumulated information acquired through this app can be of help to medical staff in determining more efficient diagnosis and treatment management, which can contribute to the formation of medical artificial intelligence algorithms.

However, considering that the actual clinical setting or the characteristics of a high-risk mother are a more complicated process through various situations and changing physical conditions, this smartphone app will not replace the medical staff in the actual field. Nevertheless, there is no doubt that this app will be a great tool for medical staff, guardians, and patients to collaborate by playing an auxiliary role in a healthy life and prevention of disease via innovative medical technology. In the future, it will be necessary to establish a continuous algorithm through collaboration between obstetricians and gynecologists, preventive medicine, psychologists, and IT experts, and to discuss the direction of use and connection of smart medical technology. In addition, smartphone-based apps using the currently configured items will require clinical verification through various studies, including actual clinical studies, to secure external validity in the future [27]. Therefore, empirical research or analysis of this smartphone application should be conducted in follow-up studies.

